### Interventions

Participants will be randomly divided into two groups (Fig. 1 and Fig. 2), called PNE + CH + OMT (intervention group) and PNE + CH + sham therapy (control group). For both groups, the participants will be submitted to PNE based on information from the book “Explain Pain” and CH [11, 15]. The intervention group will receive the same approach and additionally four OMT visits and the control group, sham therapy. For both groups, the meetings of OMT or sham therapy will be distributed in 30 min and 20 final minutes with a focus on education with PNE and CH. I All procedures (control and intervention group) will be carried out individually, once a week, with an interval of at least 7 days. Participants who cannot attend on the pre-scheduled days will be offered new dates within the study period, in order to avoid sample loss. All participants will be encouraged to report adverse events at any time to any researcher during the conduction of this study.

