**Discussion:**

The guidelines have been encouraging multimodal, biopsychosocial approaches for patients with CLBP; in this sense, the results of this study can help clinicians and researchers in the implementation of a model of treatment strategy for these patients. In addition, patients may benefit from approaches with minimal risk of deleterious effects and low cost. In addition, it will enable the addition of relevant elements to the literature, with approaches that interact and do not segment the body and brain of patients with CLBP, allowing new studies in this scenario.

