Osteopathic manipulative treatment (OMT) is a hand-on part of osteopathic approach and a modality used in the treatment of LBP. Dal Farra et al., in a meta-analysis, presented strong evidence on pain reduction and improvement in function in LBP patients undergoing OMT [8]. The results presented by the systematic review by Louw et al. showed that, combining movement therapies, such as manual therapies, with education processes, it potentiated the effects on pain, function, disability, and psychosocial factors and also enabled improvement in movements and decreased use of health services in patients with chronic musculoskeletal pain [9].

Buttler and Moseley developed a method called pain neuroscience education (PNE). Addressing concepts of neurophysiology, neurobiology, representation, and meaning of pain, PNE aims to desensitize the neural system, contrary to the traditional anatomical and biomedical model [10]. In association with educational strategies, Rizzo et al. showed that clinical hypnosis (CH) enhances the results of education processes in patients with CLBP in the short and medium terms [11]. Thompson et al. in a meta-analysis totaling 3632 patients showed the effectiveness of CH as a pain re-education technique, producing moderate to great analgesia for all pain outcomes [12].

In view of the absence of standards in isolated allopathic or complementary treatments in the effectiveness of the treatment of CLBP, the growing number of researches in these areas of activity, and the absence of high-quality clinical trials that combine the aforementioned therapies in the management of this condition, our research is justified. This study aims to know whether OMT associated with PNE and CH is effective in the pain and disability of patients with CLBP in the short and medium terms or if the PNE and CH are sufficient in the management of these patients. We hypothesize that the combination of a physical approach such as OMT with PNE and CH can bring more benefits to this population, improving pain levels and reducing disabilities, in the short and medium terms.

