Based on the findings of the clinical evaluation, techniques addressing the musculoskeletal systems will be performed at each meeting [18] and/or visceral with direct anatomical correlation with the lumbar [18]. In the musculoskeletal system, the lumbar segment, pelvis, sacrum, and lower limbs will be addressed; these structures are directly connected by the lumbosacral plexus. The techniques used in these segments will be myofascial techniques and joint techniques. Myofascial techniques are techniques directed at the fascia or muscle and through approaches that use continuous palpatory feedback in order to assess and alleviate the somatic dysfunctions involved. Articulation techniques are direct manual techniques that impose movements that can be of low or high speed and low or moderate amplitudes in order to improve joint function. Visceral manipulation will be used in abdominal areas that might be in relationship with the ganglia of the lumbar area, namely renal aortic ganglion (kidneys and gonads), superior mesenteric ganglion (duodenum, jejunum, ileum, cecum, appendix, ascending colon and half of the transverse colon), and inferior mesenteric ganglion (distal part of the transverse colon, descending colon and rectum) [19]. This approach is characterized by manual techniques for diagnosing and treating the viscera and their supporting structures to improve their physiological function [19]. All manual approaches delivered will be recorded in the case report file (CRF).

It is noteworthy that the OMT will be applied only to participants randomly allocated to the intervention group, that is, they will receive OMT in addition to the PNE + CH in the four meetings.

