### Compliance participation

Participants will be encouraged to bring doubts about the information provided in the previous consultation, and at the beginning of each one, the possibility of doubts regarding the education in neuroscience of pain discussed above will be open. In addition, a review of the topics already discussed will be carried out. Also at that moment, the participants will be asked about the practice of self-hypnosis at home and the other orientations carried out. In this way, we aim to guarantee the participation and adherence of the volunteers in the proposed procedures.

Participants will be asked about the need for co-interventions, such as the use of analgesics or other physical therapies, during the intervals between consultations. All information must be informed to the researchers.

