#### Main outcome

Pain and disability will be the main outcomes of the study. Pain will be evaluated through the numerical pain scale, where the participant will be asked about their perception of pain suffered in the last week and will assign a value to it, ranging from 0 to 10, where 0 indicates no pain and 10 indicates worst pain ever felt [11, 23]. Pain will also be assessed by pressure threshold using a pressure algometer device (Fnd-50, PIAB 50-n, Italy) in the lumbar region. The assessment will be conducted specifically on the paraspinal muscles bilaterally at the L1 to L5 levels. Three measurements will be performed at the same point, and the average of the values will be calculated [24]. The distal end of the device will be positioned perpendicularly on the evaluated surface, and constant pressure of 2.55 kg will be applied. Participants will be instructed to indicate the moment when the sensation of pressure changes to a sensation of pain and the value will be recorded. The pain threshold will be defined in kilogram-force (kgf/cm^2^), through the minimum pressure necessary to induce pain in the evaluated region. Still as the main outcome, disability will be evaluated through the Oswestry Disability Questionnaire translated and validated for the Brazilian population [25] composed of ten questions that assess pain intensity and the effect of pain on activities of daily living and classify the individual as minimal (0–20%), moderate (21–40%), severe (41–60%), disability (61–80%), or bed-bound (81–100%) [26].

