#### Secondary outcomes

As secondary outcomes, the patient’s global impression of improvement, central sensitization, and biopsychosocial factors will be evaluated. The patient’s overall impression of improvement will be assessed using the 11-point Improvement Percentage Scale, ranging from − 5, indicating “much worse,” to 0 indicating “no change” to +5 “completely recovered” [23, 27], i.e., higher scores correspond to greater recovery. Central sensitization will be evaluated using the Central Sensitization Questionnaire translated and validated for the Brazilian population [28] composed of two parts (A and B), where part A contains 25 statements, scored on a Likert scale from 0 to 4 points, whose final score can vary from 0 t o100 points, with values closer to 100 indicating a greater degree of central awareness. Part B contains a list of 10 medical diagnoses related to central sensitization syndrome, and the subject is asked about the presence/absence and year of diagnosis. Biopsychosocial factors will be evaluated using the STarT Back Toll questionnaire [29] which classifies the risk of poor prognosis of individuals with LBP in the presence of physical and psychosocial factors and is composed of nine items related to referred pain, dysfunction, comorbidities, and psychosocial factors such as catastrophizing, fear, anxiety, and depression that classify the individual as low, medium, and high risk.

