## Discussion

### Potential impacts and significance of the study

The study will provide information on the effectiveness of osteopathic manipulation combined with education in pain neuroscience and clinical hypnosis on pain parameters, disabilities, and biopsychosocial aspects of patients with DLC, verifying the importance or not of including “hands on” approaches.

The guidelines have been encouraging multimodal, biopsychosocial approaches for patients with CLBP; in this sense, the results of this study can help clinicians and researchers in the implementation of a model of treatment strategy for these patients. If the study hypothesis is proven, patients may benefit from approaches with minimal risk of deleterious effects and low cost. In addition, it will enable the addition of relevant elements to the literature, with approaches that interact and do not segment the body and brain of patients with CLBP, allowing new studies in this scenario.

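### The only adverse-event collection described is volunteered reporting, yet the Discussion and abstract speak of minimal risk, which neither the efficacy hypothesis nor about 30 OMT participants could support

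*Protocol article*

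**What the plan says.** **Collection of harms.** The Interventions section has one sentence on adverse events: "All participants will be encouraged to report adverse events at any time to any researcher during the conduction of this study". The article gives no other rule for them.

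**What is actively asked.** Under Compliance participation, at the start of each consultation, "the participants will be asked about the practice of self-hypnosis at home and the other orientations carried out". The same section has participants asked about analgesics and other physical therapies used between consultations. Harms are not named among these questions.

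**Outcomes.** "Pain and disability will be the main outcomes of the study". For the secondary outcomes, "global impression of improvement, central sensitization, and biopsychosocial factors will be evaluated", and heart rate variability is added. No harm is listed.

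**Exposure and blinding.** The OMT section includes joint techniques that "impose movements that can be of low or high speed and low or moderate amplitudes", as well as visceral manipulation. The sham arm receives superficial touch. One researcher delivers all procedures (Study design and participants), and the Blinding section says that this person cannot be blinded.

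**Wording on risk.** The hypothesis at the end of the Background concerns "improving pain levels and reducing disabilities, in the short and medium terms". Under Potential impacts and significance, the Discussion says: "If the study hypothesis is proven, patients may benefit from approaches with minimal risk of deleterious effects and low cost". The abstract's Discussion says, with no condition, that "patients may benefit from approaches with minimal risk of deleterious effects and low cost".

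**The concern.** There are two linked problems.

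First, reporting that depends on the participant coming forward tends to under-count minor and transient reactions. Here it may also do so unequally. The person whom participants meet at all four sessions knows the allocation, and the physical exposure differs between arms. A difference between OMT and sham in reactions after sessions could then be blurred or distorted.

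Second, the Discussion makes low risk part of what patients gain if the hypothesis is proven. Proof of an effect on pain and disability carries no information about risk. A short or empty list of volunteered events could later be taken as confirming the phrase. The article plans to pass its results to clinicians, patients and social media, so the phrase would travel with them.

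**Working it through.** The article gives no adverse-event rate, safety margin or safety power, so there is no figure of its own to reproduce. The check has three parts.

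**1. Do the scheduled measures stand in for adverse-event collection?**
Inputs: four weekly sessions; pain asked over the last week (Main outcome); assessments at M0, M1 immediately after the last meeting, and M2 four weeks later (Outcomes). Take session 1 as day 0 with exact 7-day spacing.
- Sessions fall on days 0, 7, 14 and 21. M1 is on day 21, and M2 on day 21 + 28 = 49.
- Pain recall at M1 covers days 14 to 21. Pain recall at M2 covers days 42 to 49.
- A reaction after session 1 or 2 that has resolved by day 14 is outside both windows. A reaction that begins after M1 and resolves before day 42 is also outside both.
- A reaction after session 3 is inside the M1 window, but only as part of one pain score.
- Sessions are at least 7 days apart, so longer spacing moves even session 3 towards or beyond the edge of the M1 window.

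The global scale does run down to much worse, but it gives a single net rating and not events. The exclusion of participants whose symptoms increase (Study design and participants) must also be reconciled with the analysis of all randomized participants (Statistical analysis). As written, it could remove from observation those who react badly.

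**2. What could the OMT arm show about risk?**
Inputs: 60 participants (Sample size) at 1:1 (Study design), so about 60/2 = 30 in the OMT arm. Simple randomisation does not guarantee exactly 30.

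Upper limit for the per-participant risk with zero events and complete capture: 1 − α^(1/n).
- One-sided 95%, n = 30: 1 − 0.05^(1/30) = 9.5%.
- Two-sided 95%, n = 30: 1 − 0.025^(1/30) = 11.6%.
- With n = 26 (half of the 52 before the loss allowance): 10.9% and 13.2%.

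These limits reflect sample size alone. Better questioning would not change them.

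**3. What does incomplete capture add?**
Let c be the probability that an affected participant's event is reported. The documents give no value, so c is an assumption and is shown over a range. The risk of a reported event is c × p, so the limit on the true risk p is the limit above divided by c. The last column assumes, for illustration, a true risk of 5%, and gives the chance of an empty list as (1 − 0.05c)^30.

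| Capture c (assumed) | One-sided 95% limit on true risk, zero reports, n = 30 | Chance of zero reports if true risk is 5% |
|---|---|---|
| 100% | 9.5% | 21% |
| 50% | 9.5% / 0.5 = 19% | 47% |
| 30% | 9.5% / 0.3 = 32% | 64% |
| 20% | 9.5% / 0.2 = 48% | 74% |

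The step from the first row to the lower rows is the cost of passive reporting. The first row is the cost of a small arm.

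**The case against.** **The article is condensed.** It does not say that volunteered reporting is the only route. The schedule figure is not shown, the CRF fields cannot be seen, and adverse-event forms and safety tables are commonly left to the full protocol. This stands against the stronger reading that harms are collected only if volunteered, which a reader might infer but which the document does not state. It does not dispose of the point. The article describes in some detail what staff ask at each consultation and what goes into the CRF, and the one method that it gives for harms is a passive one.

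**The low-risk phrase is not a conclusion of the plan.** A reader might infer that the trial intends to declare safety if efficacy is shown. The documents do not support that. The phrase is a hedged remark about potential impact, placed beside one on low cost, and no objective or analysis concerns safety. The abstract does not tie it to the hypothesis at all. What remains is that the Discussion's conditional sentence does not follow from an efficacy-only hypothesis.

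**Worsening is partly observed.** A blinded evaluator measures pain and disability at set times, questions about analgesics may reveal a reaction, and that evaluator is also among the researchers to whom events can be reported. So it is too strong to say that all reactions would be missed. By the dates above, short-lived ones largely would be.

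**The 9.5% and 11.6% limits do not measure passive reporting.** This is correct. They hold under full capture, and only the values for lower capture, which rest on an assumption, bear on the collection method.

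**Conclusion.** The point holds as a cheap improvement to the harms method and a correction of wording. The primary and secondary analyses and the sample size are unaffected.

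Volunteered reporting to any researcher is the only route described, in a trial with an unblinded therapist, physically different exposures in the two arms, and existing contacts at which a question could be asked. The low-risk wording has no support from the efficacy hypothesis. The data could not supply it either: an empty list in about 30 OMT participants is compatible with a true risk of up to 9.5% (one-sided) or 11.6% (two-sided) at best, and of about 19% to 48% (one-sided) if capture is between 50% and 20%.

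This rests on about 30 participants in the OMT arm, on one capture probability common to all affected participants, and on the unshown figure and CRF not already providing solicited collection. If they do, the first half is settled by saying so, and the wording still needs correction.

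**What to change.** 1. Add one standard open adverse-event question, in the same words in both arms, to the questions under Compliance participation at sessions 2 to 4, and ask it again at M1 and M2. Asking at sessions 2 to 4 covers the intervals after sessions 1 to 3. M2 covers the period after session 4. At M1 and M2 the blinded evaluator can ask it.
2. Record the answer in the CRF, with onset relative to the session, severity and duration. Report the number of participants with events by arm, with confidence intervals.
3. In the Discussion, detach the low-risk wording from proof of the hypothesis. There and in the abstract, make it conditional on the harms data collected and their precision.
4. The Trial status section describes recruitment as ongoing. Record the date on which the question is introduced, because counts before and after it are not comparable.

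The cost is one question at visits that already take place, one CRF item, two reworded sentences, and notice to the ethics committee if the change counts as substantial under Protocol amendments. The downside is that more minor events will be recorded in both arms.

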**Fig. 1 Fig1:**
[figure not shown]
Study flowchart. PNE, pain education and neurosciences; CH, clinical hypnosis; OMT, osteopathic manipulative treatment; G1, intervention group; G2, control group

**Fig. 2 Fig2:**
[figure not shown]
Schedule for enrollment, interventions and assessments

### Pain neuroscience education (PNE)

Participants will receive four 20-min sessions, with an interval of 7 days between meetings, where the researcher will address PNE using metaphors, stories, and clear explanations about the neurophysiology of pain. Subsequently, the patient will be submitted to brief hypnotic experiences on the subjects taught in the PNE for greater fixation. At the end of the first consultation, participants will receive a 42-page printed booklet containing information covered in each meeting based on the book “Explain Pain” [15] and on their electronic devices, a 5-min video containing guided self-hypnosis performed during the session. Participants will be encouraged to read the information in the booklet and to practice guided self-hypnosis at home daily, between meetings [11]. The topics addressed at each meeting are described below.*First consultation*: The PNE theme to be addressed will be “Pain is a normal experience.” At the end of this explanation, participants will be subjected to hypnotic experiences to suggest openings for change, pointing out that the brain has many capacities that can be used to create comfortable experiences. Brief suggestions for exploring the capacities for relaxation, dissociation (body and mind), analgesia, regression, and previous pleasurable experiences will be addressed at this meeting.*Second consultation*: “Alarm system, its components and functions, in addition to the modulation of messages at the column level” will be the theme of the PNE at this meeting. In addition, two hypnotic experiments will be carried out, the first idea being expressed in the book Explain Pain - “Sensors are often replaced by new ones,” whose objective is to offer hypnotic experiences so that this adaptation in the sensors is possible. The second hypnotic experience will be related to the descending inhibitory modulation content at the spinal cord level, suggesting adapted hypnotic analgesia, inviting participants to experience analgesic sensations in their body.*Third consultation*: The PNE theme will correspond to “Changes in the central alarm system and the systemic pain response.” Next, two hypnotic experiments will be performed, the first linked to the idea that “the brain can receive amplified messages from the tissues, even when there is nothing wrong with the structure of the body,” including suggestions to lessen the discomfort of pain by inviting the patient to experience situations of comfort even in the face of some sensations in the body. The second experience will relate to the idea “the brain orchestra can play a different song.” We will offer sensory substitution suggestions, which invite participants to experience a comfortable sensation of their hands spreading to other parts of the body.*Fourth consultation*: The theme of this last PNE meeting will be “Understanding that injury is not the same as pain and education about gradual exposure.” In addition, in this last meeting, three hypnotic experiences will be given. The first will be a deep relaxation suggestion, in which participants will be asked to relax every muscle in their body. The second will be an “age regression and progression” experience, in which participants will be invited to bring adaptive responses to past or future pain into the present. Both experiences reinforce the importance of physical movement as a way to increase the benefits. The last hypnotic experience will offer a metaphor to help participants deal with negative thoughts throughout the day.

### Clinical hypnosis (CH)

The procedures for the hypnotic experiences performed right after the PNE will be divided into two parts, being the first the access to the state of consciousness that will facilitate the opening for changes. In this induction state, the researcher will invite the participant to focus their attention on a specific experience which may be the researcher’s voice or the participant's own breathing. In this state of focused attention and inhibition of critical thinking, they will be advanced to the second phase, which are suggestions for change. At that moment, specific therapeutic changes will be suggested, such as changes in sensations, behaviors, and thoughts that influence the perception of pain, based on the theme of each protocol consultation [16] previously described.

